## 11. APPENDICES

1. Advertisement(s): please see appended PICF
2. Data collection sheet / Case Report Form: please see appended data collection form

# **Randomised, double-blind clinical trial comparing IN and IM Naloxone for suspected opioid overdose**

## **1. BACKGROUND**

### **1.1 DISEASE BACKGROUND**

Drug overdose is a leading cause of death among people who inject drugs. The Sydney Medically Supervised Injecting Clinic (MSIC) was established in 2001 with the primary aim of reducing the morbidity and mortality of drug overdoses in the local area. Within the first nine years of opening, the MSIC had treated over 3000 acute opioid overdoses on site without a single fatality. Overdose management protocols are in place for nursing staff to administer intramuscular Naloxone, as well as provide external airways resuscitation and oxygen, for clients who overdose within the MSIC. Due to the high frequency of opioid overdose routinely treated onsite, and the experienced staff who manage them, the MSIC provided a unique and ideal setting to investigate alternative Naloxone administration routes.

IM and intravenous Naloxone are currently the standard modes of emergency treatment for an opioid overdose, however pharmacology data indicate that Naloxone is 100% bioavailable through the nasal mucosa. Naloxone can be sprayed into the nose via a mucosal atomisation device and evidence indicates that IN Naloxone may not only be as effective a route of administration as IM administration, but also a practical and realistic alternative. There have been a number of previous studies examining IN Naloxone. These have generally been cohort studies with only two previous randomised trials neither of which were double-blinded.

The first randomised trial used a large volume of fluid for intranasal administration which may have limited efficacy. The subsequent trial showed a slightly higher rate of 'rescue' Naloxone given to those patients whose initial dose was delivered intranasally. The authors felt that this may have been due to the non blinded nature of the study, with the additional dose being a subjective decision dependent of individual paramedic's comfort in waiting for a response.

### **1.2 RATIONALE FOR PERFORMING THE STUDY**

The aim of this study is to determine whether Naloxone, an opioid reversal agent, is as effective for the treatment of acute opioid overdose when administered via the intranasal route compared with the intramuscular route. The term 'opioid' refers to a class of drugs that includes heroin, and the prescription medications oxycontin and morphine. Injection of Naloxone into a muscle is currently the standard method of emergency treatment for an opioid overdose on site at MSIC. However, Naloxone can be administered as an intranasal (IN) spray using a 'mucosal atomisation device'. Evidence suggests that IN Naloxone may be an effective and practical alternative. The significant benefits of IN administration include removing the risk of needlestick injury (and thus any blood borne virus transmission risk) to treating personnel. This is particularly relevant to ambulance officers and paramedics, as well as other emergency health care workers, such as in the hospital emergency department setting.

Additionally, given the ease of administration and reduced issues regarding disposal of used needles, the availability of IN Naloxone may potentially be extended. This

may include non health care workers who regularly deal with opioid overdose in community settings, and drug users' peers, who are likely to be present in the event of an overdose.

## 2 STUDY OBJECTIVES

### 2.1 PRIMARY OBJECTIVE

- The aim of this study is to determine whether IN Naloxone is as effective as IM Naloxone for the treatment of an acute opioid overdose.

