## 3 STUDY DESIGN

### 3.1 DESIGN

- Prospective, randomised, double-blinded, placebo-controlled clinical trial.

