## 8 STATISTICAL CONSIDERATIONS

Recently, the study findings of a RCT comparing IN and IM Naloxone have been reported. In that study, requirement for a secondary dose of Naloxone was reported as IN:18% vs IM:4%. We estimate (using JavaStat) that we would need a sample size of 99 per group to achieve adequate power (power=0.8, with 95% confidence) to detect a difference of 14% in requirement for secondary Naloxone.

Descriptive analyses (proportion, median, effect size difference with 95% confidence intervals) will be conducted to compare demographic characteristics and over-dose related variables for the two groups by allocation (IN and IM) (e.g., age, gender demographic data, prior drug use, previous alcohol use, etc).

Primary outcomes will be compared by univariate analysis including odds ratio with 95% CI, hazard ratio (HR) and chi-square analysis. Response time will be compared using a Kaplan-Meier survival curve. A clinically significant difference in response time will be defined as two minutes.

For cases in which response times are not recorded on patient recovery, and subsequent discharge from the treatment room, a default figure of 10 minutes will be recorded.

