## Statistical analysis Plan - final

Analyses will be conducted in accordance with the International Conference on Harmonization E9 statistical principles [Lewis, 1999], and reported according to the CONSORT recommendations [Moher et al, 2001; Hopewell et al, 2008]. An intention-to-treat analysis will be performed for all participants who were randomized to receive either mode of treatment (IN and IM administration).

Descriptive analyses will be conducted to compare trial arms (IN and IM) for observed differences in demographics and other important clients' characteristics.

As the trial progressed it was noted that there were several individuals who experienced multiple overdoses who were randomized into the study, introducing clustering. Therefore the main analysis for comparing the incidence rate of secondary naloxone administration mode (IN and IM) will be performed using Generalized Linear Mixed Effects (GLMM) analysis [McCulloch, 2001] for a binary outcome variable with a logistic link function to account for within-client clustering effects because of the multiple overdoses. A Generalized Estimating Equation (GEE) technique with unstructured covariance pattern will be implemented for this purpose. Odds ratio (OR) and 95% confidence interval (CI) will be reported as intervention impact, as per the original analysis plan.

For secondary time to event outcomes medians and 95% CIs at each study arm and Kaplan-Meier survival plots will be reported as descriptive measures. Cox proportional hazards regression models, with shared Gamma frailties to account for within-client clustering effects, will be used to compare between group hazard rates. Hazard ratio (HR) and 95% CI will be reported as intervention impact as per the original analysis plant. We will explore the proportional hazards assumption through visual inspection of survival and hazard plots.

In order to fully explore the effects of repeat presentations, secondary analyses involving only the first overdose of clients will be conducted using analogous methods for primary binary (logistic regression) and secondary time to event (Cox proportional hazards) outcomes. All analyses will be carried out using Stata (version 15; Stata, College Station, TX).

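### The aim is to learn whether intranasal is as effective as intramuscular naloxone, but no margin, hypothesis type or decision rule links the planned difference analysis to that conclusion

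*Supplement*

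**What the plan says.** **Objective.** Section 2.1 of the final protocol has one objective, to "determine whether IN Naloxone is as effective as IM Naloxone for the treatment of an acute opioid overdose". Section 1.2 gives the same aim. Section 3.1 describes the design as "Prospective, randomised, double-blinded, placebo-controlled clinical trial" and does not say whether the comparison is for superiority, non-inferiority or equivalence.

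**Sizing.** Section 8 takes rates of 18% (IN) and 4% (IM) from an earlier randomised trial. It asks for 99 per group at power 0.8 and 95% confidence "to detect a difference of 14% in requirement for secondary Naloxone".

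**Analysis.** Section 8 compares primary outcomes by odds ratio with 95% CI, hazard ratio and chi-square. The final SAP moves the main analysis of secondary naloxone to a logistic model that allows for repeat overdoses in the same client. It adds: "Odds ratio (OR) and 95% confidence interval (CI) will be reported as intervention impact, as per the original analysis plan".

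**Thresholds.** The only clinically significant difference defined is two minutes, for response time. The SAP treats time-to-event outcomes as secondary, and the two minutes are tied to no test or interval rule. No threshold is given for secondary naloxone.

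**Background.** Section 1.1 reports the view of the earlier trial's authors that the excess of rescue doses after intranasal naloxone may have arisen because "this may have been due to the non blinded nature of the study, with the additional dose being a subjective decision" was involved.

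**The concern.** An aim of showing that one route is as effective as another is met by excluding an important deficit. A test built to detect a difference does not do that: failing to reject says only that the data are compatible with no difference, and they may be equally compatible with a large one. The confidence interval carries the needed information, but only if someone has said beforehand how large an excess of rescue doses is too large.

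An analyst who follows the SAP exactly will produce an odds ratio and its interval, and will then have no rule for saying whether the objective was met. A margin chosen after the result is known carries little weight. An odds ratio alone also puts no bound on the absolute excess of rescue doses. Section 1.2 looks ahead to use by non-health-care workers and drug users' peers, so an unsupported claim would have consequences.

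**Working it through.** **1. The plan's own figure.** Inputs from section 8: p1 = 0.18, p2 = 0.04, d = 0.14, power 0.80, 95% confidence. The plan does not state sidedness; I assume two-sided 0.05. The mean rate is 0.11.

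- n = [1.96·√(2·0.11·0.89) + 0.842·√(0.18·0.82 + 0.04·0.96)]² / 0.14² = (0.867 + 0.363)² / 0.0196 = 77.2, so 78 per group.
- With continuity correction: (77.2/4)·[1 + √(1 + 4/(77.2·0.14))]² = 90.9, so 91 per group.
- One-sided versions give 61 and 75.

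None of these gives 99. At 99 per group, power for 18% against 4% is 0.869 (exact, Fisher), 0.889 (normal approximation) or 0.916 (exact, chi-square). The stated number is therefore conservative. The calculation is of the kind used to detect a difference.

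**2. What a non-significant result can leave open.** Suppose the trial observes 11/99 (11.1%) rescue doses with IN and 4/99 (4.0%) with IM. These are invented results, treated as independent episodes.

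- Chi-square = 198·(11·95 - 4·88)² / (99·99·15·183) = 3.53, p = 0.060.
- Risk difference = 7/99 = 7.1 points.
- Wilson limits: IN 6.3% to 18.8%; IM 1.6% to 9.9%.
- Newcombe lower limit: 0.0707 - √[(0.1111 - 0.0632)² + (0.0993 - 0.0404)²] = -0.005.
- Newcombe upper limit: 0.0707 + √[(0.1881 - 0.1111)² + (0.0404 - 0.0158)²] = 0.152.

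The result is not significant at 0.05, yet the interval of -0.5 to +15.2 points still contains the 14-point gap on which the trial was sized.

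**3. What 99 per arm could support as a non-inferiority comparison.** The documents give neither a margin nor an expected common rescue rate, so this is an assumed range. With equal true rates p, one-sided 0.025 and 80% power, the smallest margin is (1.96 + 0.842)·√(2p(1-p)/99).

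| Common rescue rate | SE (points) | Smallest margin for 80% power (points) |
|---|---|---|
| 4% | 2.79 | 7.8 |
| 10% | 4.26 | 11.9 |
| 18% | 5.46 | 15.3 |

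These figures assume independent episodes. The SAP acknowledges repeat overdoses by the same client, so precision may be lower; the documents give no figure from which to compute the loss.

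**The case against.** **The wording may be plain language.** To determine whether can be read as a two-sided question, and no section claims non-inferiority. This is fair: the plan can validly conclude that intranasal is worse. It has no route to the affirmative answer, though, and the mildest remedy is then to reword the objective.

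**The SAP does report confidence intervals.** This is also right. A reader can see from them which effects are not excluded. A reader might infer that the plan could never inform the claim, or that the investigators intend to read non-significance as equivalence. The documents support neither: they give no rule for interpretation at all, and the planned interval could be judged against a margin if one were pre-specified. Misreading is a risk left open.

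**The 14 points are not a stated important difference.** Correct. They are the gap observed in an earlier trial, and section 8 does not call them clinically important. They serve here only as a reference point, and no particular margin follows from them.

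**The gap may be smaller under blinding.** It is tempting to say that the protocol itself expects less than 14 points. Section 1.1 reports a hedged view of the earlier trial's authors. That the true gap is smaller in this double-blind trial would be a further inference, and the point does not depend on it.

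**The sample size may be adequate.** It may well be. A reader might infer that about 200 participants are too few, but whether they are depends on a margin and a rescue rate that the documents do not give.

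**Conclusion.** The concern holds in the latest protocol and SAP. The sole objective asks whether intranasal is as effective as intramuscular naloxone. The sizing and analysis address whether the routes differ, and nothing connects the second to the first. Followed exactly, the plan can show a difference, but it has no pre-specified basis for its own affirmative conclusion.

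The size of the problem is shown by the illustration: p = 0.06 alongside an upper limit of 15.2 points. This rests on invented counts at the planned 99 per arm and on independence between episodes.

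That 99 per group is not reproduced by the standard formulas is a side matter. The error is on the safe side and does not bear on the main point.

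**What to change.** Amend the protocol (sections 2.1 and 8) and the SAP in one of two ways.

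- **(a) Keep the aim.** Pre-specify a clinically justified margin for secondary naloxone, smaller than 14 points. Claim that intranasal is as effective only if the upper limit of the two-sided 95% CI for the risk difference (IN minus IM, marginal, clustered on client) lies below it. The margin needs a clinical argument, which the documents do not supply.
- **(b) If no margin can be justified,** restate the objective as testing for a difference.

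In both cases, state that non-significance alone does not support the claim, and report the risk difference with its 95% CI beside the odds ratio. Restate the sizing sentence: 18% against 4% at 80% power needs 78 per group (91 with continuity correction), and 99 gives power of about 0.87 to 0.92. Under (a), add the power for the chosen margin, with an allowance for clustering.

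**Cost.** Option (b) needs changed wording and one extra marginal estimate. Option (a) needs the same plus the work of justifying a margin, and it may need more participants if the margin is tight. The claim also becomes harder to make if rescue rates are near 10%, where 99 per arm reaches 80% power only for margins of about 11.9 points or more.

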## 3 STUDY DESIGN

### 3.1 DESIGN

- Prospective, randomised, double-blinded, placebo-controlled clinical trial.

### 3.2 NUMBER OF PARTICIPANTS

- Approximately 200

### 3.3 NUMBER OF CENTRES

- Single-site study

### 3.4 DURATION

- November 2010 – October 2012
- Participants will be consecutively enrolled during this period. We estimate at current rates of overdose requiring Naloxone, eighteen months to two years will be required to achieve a sample of 200 participants.

## 4 PARTICIPANT SELECTION

### 4.1 INCLUSION CRITERIA

- Age range: 18 years and over
- Weight: not defined
- Height: not defined
- Disease status: All clients with symptoms/signs of an opioid overdose requiring Naloxone administration will be eligible for entry. This is based on existing and approved MSIC protocols and clinical criteria for overdose (reduced level of consciousness as measured by the Glasgow Coma Score, pinpoint pupils, respiratory depression and/or reduced oxygen saturations as measured by pulse oximetry).

### 4.2 EXCLUSION CRITERIA

The research design specifically excludes pregnant women, the human foetus and individuals under the age of eighteen. Sydney MSIC specifically excludes these individuals from utilising the MSIC by the following procedure:

- If it is suspected by MSIC staff that a client may be pregnant, they are referred to a local drug and alcohol programme where they undergo a pregnancy test. The results are then returned to MSIC.
- If it is suspected a potential client may be under eighteen years old, formal ID is requested of the potential client by MSIC staff. If the person is over eighteen, a copy of the ID is kept on file. If the person is under eighteen, they are referred to a local drug and alcohol service.
- Anyone who presents as already intoxicated from alcohol or other drugs, anyone accompanied by a child and anyone who has not previously injected drugs are already excluded from using the MSIC according to the internal management protocols required by legislation.
- Probable incidental recruitment may include people whose primary language is other than English, people in existing dependent or unequal relationships, people with a cognitive impairment, intellectual disability or a mental illness and people from Aboriginal and Torres Strait Islander backgrounds.

## 5 STUDY OUTLINE

### 5.1 STUDY FLOW CHART

[figure not shown]

## 5.2 INVESTIGATION PLAN

| Enrolment Visit                                  | Client 1 | Client 2 | Client 3 | Client ... | Client 200 |
|--------------------------------------------------|----------|----------|----------|------------|------------|
| Informed Consent                                 | ✓        | ✓        | ✓        | ✓          | ✓          |
| Inclusion / Exclusion criteria                   | ✓        | ✓        | ✓        | ✓          | ✓          |
| Narcan Administration                            | ✓        | ✓        | ✓        | ✓          | ✓          |
| Vital signs collected                            | ✓        | ✓        | ✓        | ✓          | ✓          |
| Adverse Event & Serious Adverse Event Assessment | ✓        | ✓        | ✓        | ✓          | ✓          |

#### 5.4 RECRUITMENT AND SCREENING

- Recruitment: all MSIC clients are potential participants for this study, as all MSIC clients may potentially experience opioid overdose while using the centre. Flyers will be placed around MSIC notifying clients of the study.
- Screening: All clients with symptoms/signs of an opioid overdose requiring Naloxone administration will be eligible for the study. This is based on existing and approved MSIC protocols and clinical criteria for overdose include:
  - glasgow coma score < 13
  - pinpoint pupils
  - respirations < 10/min and/or
  - reduced oxygen saturations (< 95%).

#### 5.5 INFORMED CONSENT PROCESS

We have used Section 2.2.5 of the National Statement on Ethical Conduct in Human Research to guide us in a method of obtaining oral consent. Informed consent will be obtained from the participants in the following way:

- By ensuring that the trial is comprehensively advertised at MSIC;
- Any newly registering clients will be provided details of the trial;
- By asking the clients once if they consent to participate and offer any further information requested;
- When a client declines to participate this will be flagged on the database. This list of clients will be regularly reviewed at clinical case reviews so that all staff are familiar with the clients who do not want to participate;
- If a consenting client is enrolled, they will be informed of their participation after the intervention. At a point that is suitable, bearing in mind the process of the client's recovery, they will be asked if they wish to withdraw that event's data from the study.

#### 5.6 ENROLMENT PROCEDURE

The participant will be enrolled into the study after the informed consent process has been completed and the participant has met all inclusion criteria and none of the exclusion criteria. Participants will then be consecutively enrolled during all operating hours of the service. All clients of the MSIC will be informed of the study

at registration. The participant will be informed of their enrollment once they have fully regained consciousness. If they decline to participate, the data will be eliminated from the database.

## 5.7 RANDOMISATION PROCEDURE

MSIC staff will manage drug overdoses using existing clinical protocols. These state that a client will receive airway management and oxygenation either via a Hudson mask or artificial ventilation (bagging) for five minutes before being assessed as to the need for Naloxone. Where a client's response after five minutes is inadequate, Naloxone will be administered by a registered nurse in accordance with existing standing orders from the Medical Director.

Study participants will receive a random allocation of Naloxone in one of 2 forms:

- Active intranasal Naloxone and intramuscular placebo, or
- Intranasal placebo and active intramuscular Naloxone.

Study packs will be pre-prepared and contain two clearly labelled vials – 1) Intranasal - Naloxone 800mcg/1mL or placebo (1mL) for IN administration and 2) Intramuscular - 800mcg/1ml or placebo for IM administration. The vials will be labelled as intranasal and intramuscular, therefore the person administering the drugs will be blinded to the treatment arms. As per MSIC protocol, two staff members will attend the patient during treatment of opioid overdose. A third attending staff member will record the participants' vital signs on a chart. The chart is currently in use for overdoses.

To minimise potential bias, the order in which the drug will be administered will be rotated approximately midway through the study. Initially the intranasal drug preparation will be administered first, followed by the intramuscular drug preparation. Approximately midway through recruitment (e.g., after 100 enrolments), the intramuscular drug preparation will be administered first, followed by the intranasal drug preparation.

Contents of the vial for IN administration will be drawn into one syringe. Staff will attach the syringe to a MAD, and administer 0.5mL (400mcg) into each nostril, depressing the syringe rapidly to achieve adequate atomisation. In this way, each study participants will receive 0.5mL of fluid in each nostril. Supportive care/oxygenation will be administered simultaneously, in accordance with existing MSIC clinical protocols

Administration of the IM injection will be by standard practice of drawing the full 1ml into a single 5ml syringe and administering to the deltoid muscle via a 23g needle.

Any client who fails to respond adequately after ten minutes will be eligible for a second dose. This dose will be a known dose of 800mcg of Naloxone administered intramuscularly and not subject to randomisation. In this manner, all overdoses will receive the same clinical care they would have otherwise, under existing approved clinical protocols, with Naloxone administered at the same time point, in response to the same clinical criteria. The only exception will be that the need for any additional dose of Naloxone will be assessed at ten minutes post- first dose as opposed to five minutes. Importantly, all clients will be adequately oxygenated and fully monitored during this time.

Post analysis, the treatment allocations will be de-coded.

The preparation of Naloxone and placebo will be manufactured by a registered pharmaceutical company, Sypharma Pty Ltd, and will comply with national medication quality and safety standards. The complete study packs will be packed by Pharmpackpro Pty Ltd.

